**Figure 2 f2:**
[figure not shown]
Procedure of EA and operation parameters. **(A)** Schematic protocol of EA manipulation (3 times a week for 6 weeks; 30 min a session). **(B)** Locations of acupoints. **(C)** Operation parameters for lifting and thrusting. **(D)** Operation frequency of twirling and rotation.

### Counseling Group

Sub-threshold depressed participants will receive individual counseling (once a week for 6 weeks; 50–60 min a session). Counseling will be performed by licensed psychologists with more than 3 years' experience and will be conducted in the psychiatric department of the hospital. Before the trial, the psychologists will receive brief training in counseling and conduct counseling activities based on a treatment manual designed by *Mental Disorders* (35). It mainly includes two aspects: First, help participants analyze their own problems, inform them about the physical harm of psychological defects, and encourage them to overcome these factors. Second, encourage participants to do things of interest to increase excitement and improve emotional state.

### Combination Therapy Group

Participants will receive 24 sessions of EA treatment (three times a week for 6 weeks; 30 min a session) combined with individual counseling (once a week for 6 weeks; 50–60 min a session). Treatment details are the same as the EA and the counseling mentioned above.

Patients will be discouraged from any extra treatment beyond this trial requirement. If this trial does not show an obvious effect after 2 weeks of treatment (HAMD 17 scale score maintained at 7–17 points), or a patient's symptoms have worsened (HAMD 17 scale score > 17 points), we will then consider drug intervention to ensure the safety of the patients. At this point, participants will be forced to stop the trial, and relevant data will be analyzed for intention-to-treat (ITT). Prescription drugs will be assessed under the guidance of a psychiatrist. Such assessment will need to fully consider the physiological characteristics of patients, including age, physical condition, drug tolerance, presence or absence of comorbidities, and prescribing based on guidelines for depression or relevant clinical consensus.

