### Trial Objective

We suspect that EA could alleviate the clinical symptoms of patients with sub-threshold depression as well as counseling. If EA is not only the placebo, the combination therapy will have a better effect, and may reduce the risk of conversion from mild to severe, as well as help determine whether patients with sub-threshold depression will need multiple therapies in the future. If acupuncture does no effect, the combination group will have the same clinical effect as the counseling group. Therefore, the objective of this trial is to evaluate the effectiveness of sub-threshold depression treatment by comparing the effects among EA, counseling, and combination therapy, as well as to further study the mechanism of EA and counseling.

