### Participants

Participants will be recruited by advertisement and doctor referrals from psychology department clinics. Interested individuals can contact research assistants by email or phone. A series of criteria and prerequisites will be sent to the prospective volunteers for filtering the most eligible subjects. First, registration information and pre-selection query forms with Self-rating Depression Scale (SDS), Pittsburgh Sleep Quality Index (PSQI), and Self-rating Anxiety Scale (SAS) will be sent to registered volunteers. Volunteers will be required to complete the form as a first-round selection prior to scheduling a first visit. This visit will further screen and evaluate a volunteer's eligibility according to inclusion criteria (**Table 1**). Research assistants will collect signed consent forms from volunteers who meet all prerequisites and agree to participate in the trial. Patients will not be included in the study if they meet one of the exclusion criteria (**Table 2**).

**Table 1 T1:** Inclusion criteria.

No	Item	Answer
1	18<age<55	□Yes
		□No
2	Presence of ≥ 1 but < 5 symptoms required for the diagnosis of major depression as detailed in the Diagnostic Statistical Manual of mental disorders (DSM-V), including loss of enjoyment/interest, marked tiredness or reduction of energy, agitation or psychomotor retardation, feelings of worthlessness or guilt, sleep disorders, reduced concentration, loss of appetite and body weight, loss of libido, recurrent suicidal thoughts;	□Yes
		□No
3	symptoms lasting at least 2 weeks	□Yes
		□No
4	BDI-II score≥14 points (24)	□Yes
		□No
5	HAMD-17 score: 7 points ≤ HAMD total score < 17 points (25)	□Yes
		□No

**Table 2 T2:** Exclusion criteria.

No	Item	Answer
1	Patients diagnosed with depression, previous mental illness, or organic mental disorders	□Yes
		□No
2	Patients suffering from serious diseases such as heart, brain, liver, kidney, or hematopoietic system disease	□Yes
		□No
3	Women during pregnancy and lactation or women of childbearing age who have fertility intentions	□Yes
		□No
4	Patients with depressive episodes caused by psychoactive substances and non-addictive substances	□Yes
		□No
5	Patients prescribed other drugs or therapies for treating depression during the trial	□Yes
		□No
6	Individuals addicted to alcohol or other drugs	□Yes
		□No
7	Patients with strong suicidal ideation	□Yes
		□No
8	Patients who are participating in other clinical trials at the same time	□Yes
		□No

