### Observation Criteria That Would Stop the Trial

Fail to adhere to the treatment requirement;Cases with serious adverse events that are not suitable for continued treatment;Serious clinical complications that occur in other clinical trials;The progression of disease during treatment.

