### Sample Size

Sample size estimation uses a completely random design to compare multiple sample means. Target sample size was estimated using the PASS11 version, 1-β = 0.9, α = 0.05. According to a previous study (27), the mean of HAMD-17 in the psychological counseling group was 5.7, and the standard deviation was 3.13; the mean of HAMD-17 in the EA group was 5.26, and the standard deviation was 3.11; the mean of HAMD-17 in the combined therapy group was 3.4. The standard deviation was 2.97. To reduce the error, the target sample size was slightly enlarged, and a 10% dropout rate was estimated. Therefore, a sample of 46 participants will be the goal for each group in the proposed trial. A total of 138 patients will be aimed for in total.

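### The week-2 lack-of-effect rule is a HAMD-17 band covering the whole entry range, so it tests remission and not change, and patients stopped under it lose their later primary outcomes selectively

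*Protocol article*

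**What the plan says.** All references are to the protocol article.

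- **Trigger** (Combination Therapy Group, second paragraph): "If this trial does not show an obvious effect after 2 weeks of treatment (HAMD 17 scale score maintained at 7–17 points". The second limb reads "or a patient's symptoms have worsened (HAMD 17 scale score > 17 points), we will then consider drug intervention".
- **Consequence** (same paragraph): "At this point, participants will be forced to stop the trial, and relevant data will be analyzed for intention-to-treat (ITT". A psychiatrist guides the choice of drug for the individual patient.
- **Entry** (Participants, Table 1): "7 points ≤ HAMD total score < 17 points".
- **Score categories** (Outcome Measures): HAMD-17 of 0–6 is normal and 7–17 is possible mild depression. HAMD-17 and BDI-II, the primary outcomes, are scheduled at baseline and weeks 2, 4 and 6.
- **Missing data** (Statistical Analysis): an ITT analysis, with a withdrawn patient's missing data multiply imputed.
- **Allowance** (Sample Size): "a 10% dropout rate was estimated".

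**The concern.** The rule is worded as a test of whether treatment has had an effect, but its only stated criterion is a score level, and every patient meets that level on entry. The two limbs together cover every score of 7 or more. Whether a patient escapes therefore depends as much on the entry score as on the response.

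The consequence attached is exit from the trial, one third of the way through treatment. If exit also ends assessment, weeks 4 and 6 of both primary outcomes go missing because the week-2 response was poor, and more often in an arm that works less well. The comparison exposed is combined against counselling, on which Trial Objective rests its judgement of acupuncture: "If acupuncture does no effect, the combination group will have the same clinical effect as the counseling group". A criterion that does not define a change also gives the four hospitals little common ground for deciding whom to stop.

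**Working it through.** **1. The plan's own figure.** Inputs from Sample Size: means 5.7 (counselling), 5.26 (EA) and 3.4 (combined); SDs 3.13, 3.11 and 2.97; alpha 0.05; power 0.90. A one-way ANOVA with the average SD of 3.07 gives power 0.8998 at 41 per group and 0.907 at 42. Then 41/0.9 = 45.6, or 46, and 42/0.9 = 46.7, or 47. The planned 46 per group is reproduced to within rounding, and the point does not depend on it.

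**2. The band against the entry range.** This needs no assumption. Entry scores run from 7 to 16, and leaving the band by improvement means reaching 6, so the fall needed is entry score − 6.

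- Entry 7: 1 point (1/7 = 14%).
- Entry 16: 10 points (10/16 = 62.5%).
- Halved or better but still in the band: 14 to 7 (50%), 15 to 7 (53%), 16 to 8 (50%), 16 to 7 (56%).
- For entry scores 7–13, a 50% fall does leave the band.

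**3. Share in range if week-2 scores already sat at the Sample Size values.** That section gives no time point, so this is a condition and not a forecast. Share = 1 − Φ((c − mean)/SD), with c = 7, or 6.5 to allow for whole-number scores.

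| Arm | c = 7 | c = 6.5 |
|---|---|---|
| Counselling | (7 − 5.7)/3.13 = 0.415, share 0.339 | 0.399 |
| EA | (7 − 5.26)/3.11 = 0.559, share 0.288 | 0.345 |
| Combined | (7 − 3.4)/2.97 = 1.212, share 0.113 | 0.148 |

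The total is 46 × 0.740 = 34 of 138 for c = 7 and 46 × 0.892 = 41 for c = 6.5. The counselling to combined ratio is 3.0 or 2.7.

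**4. When the allowance is used up.** 10% of 138 is 13.8. 13.8/34.0 = 41% and 13.8/41.1 = 34%. So stopping about 34–41% of in-range patients exhausts it before any ordinary dropout. If only patients with no fall at all stop, the overall loss is about 1–14% (assumed baseline mean 11.5, SD 2.5–3.07, correlation 0.6).

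**5. Power and bias, combined against counselling, 46 per arm.** Reference t-test power for a difference of 2.3 with SD 3.05 is 95% with full data and 92% with 10% random loss. The simulation used 2,500 runs and normal multiple imputation on arm and week-2 score, with 20 imputations. Assumptions not in the documents: baseline 11.5, week-2 SD 3.07, correlation 0.6 between weeks 2 and 6. Shares are for c = 6.5; the first row takes them from step 3.

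| Fall reached by week 2 | In range, counselling v combined (ratio) | Power if all / half / a quarter of those in range stop |
|---|---|---|
| Full | 0.40 v 0.15 (2.7) | 87 / 92 / 95% |
| Three quarters | 0.58 v 0.36 (1.6) | 74 / 89 / 93% |
| Half | 0.75 v 0.62 (1.2) | 47 / 85 / 91% |

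With all stopped, power over the three rows is 83/66/39% at correlation 0.4 and 91/83/63% at 0.8. The mean estimate with all stopped is 2.30, 2.32 and 2.28 against a true 2.3, so there is no material bias when the imputation model is correct.

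**6. If the imputation model is wrong.** In the full-fall case with all stopped, a 1-point error in the imputed scores moves the arm difference by 0.34–0.40 if it affects counselling only. If it affects both arms, the shift is 0.339 − 0.113 = 0.23 to 0.399 − 0.148 = 0.25. It shrinks in proportion if fewer stop.

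**The case against.** Much can be said for the plan, and several parts stand.

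- **The stop looks discretionary.** Drugs are only to be considered, the score must be maintained, and a psychiatrist guides prescribing. A patient who falls from 16 to 7 fits the numbers but hardly the idea of no obvious effect. The exclusion "Patients prescribed other drugs or therapies for treating depression during the trial" suggests that those who leave are the ones actually put on drugs. The list of stopping criteria has "The progression of disease during treatment" but no item for lack of effect. A reader might infer that every patient at 7 or more at week 2 must be removed; the documents lean against that.
- **The band is not arbitrary.** It matches the article's mild category and separates remitted (0–6) from non-remitted patients. A reader might infer that it cannot tell responders from non-responders at all; that is true only of response as change, and a halving can stay in the band only from entry scores 14–16.
- **A rise from 7 to 17 is not labelled worsening,** but it meets the first limb and leads to the same action, so little turns on it.
- **Loss depends on an observed score.** Imputation can use week 2, and the simulation shows no material bias. If stopping is discretionary, in-range patients who continue also supply later data to inform it.
- **This is a condensed article,** and assessment after a stop may be set out in the full protocol. That is possible, but the article does state a consequence, and the consequence is leaving the trial and not merely the treatment.

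Discretion does not repair the criterion, because the only number given to guide it does not measure change.

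**Conclusion.** The rule is badly fixed and should be corrected. That the trigger band contains the whole entry range, and so acts as a remission test, follows from the text alone. Selective loss of week-4 and week-6 HAMD-17 and BDI-II follows if stopping the trial ends assessment, as the wording suggests; that it would be heavier in the weaker arm is likely but not certain.

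The size is open. With week-2 scores at the Sample Size values, 34–40% of counselling and 11–15% of combined patients are in range, and the dropout allowance goes once about 34–41% of all in-range patients are stopped.

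A reader might go further and infer that the trial would be badly underpowered or its result biased. The material does not support that. Power falls markedly (to 74% or 47%) only if every in-range patient stops and response is slow, which is not the reading the text favours, and those figures rest on an assumed baseline and correlation. Nor do the harms peak together: the roughly threefold imbalance belongs to the fast-response case, where power with all stopped is 87%, while at 47% the ratio is only 1.2. Bias requires the imputation model to be wrong.

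**What to change.** 1. **Separate stopping treatment from leaving the trial.** This is the change that matters most. Anyone stopped or rescued stops study treatment only. HAMD-17 and BDI-II are still taken at weeks 4 and 6, and SDS, SAS and PSQI at the scheduled follow-ups. The rescue start date is recorded. Observed scores are analysed in the randomised arm under the stated ITT, and only visits truly missed are imputed.
2. **Restate the trigger.** For example: at week 2, in all three arms, a HAMD-17 of 7 or more without a fall of at least [X] points from baseline opens psychiatric assessment for drug treatment; it does not by itself mandate a stop. The investigators set X in advance. This makes the rule measure what it claims to and helps the centres apply it alike, but stopping would still depend on response, so it does not replace item 1.

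The cost is protocol wording and keeping stopped patients in visits already scheduled; the safety route to a psychiatrist is unchanged. The downside is that scores after rescue include the drug effect and may dilute the difference between arms.

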### Safety and Adverse Events

The progress and safety data of the clinical trial will be monitored and managed by an independent Data and Safety Monitoring Committee. The committee will remind participants to report any undesirable and unexpected experiences, whether related to the intervention or not, to the research team at any time during the trial. In addition, the time of occurrence, severity, management, and outcome of these adverse events will need to be recorded on the case report forms. Common adverse events related to EA are fainting during acupuncture, local hematoma, local infection, stucking of needle, broken needle, or bending of needle. The main causes of these adverse events include poor disinfection, improper operation, improper use of needles, and unexpected reactions from patients themselves. The research team will need to explain the work to the patient before starting acupuncture. To achieve proficiency, we will conduct training about acupuncture therapy for acupuncturists. In the case of an adverse event, the researcher, in addition to providing an immediate positive treatment to the patient, will be required to complete an adverse event report and escalate the case to the staff in charge of the research center and the responsible unit for clinical research. All adverse events will be followed up from the reported date until the incident is resolved. According to the WHO Uppsala Monitoring Centre System for Standardized Case Causality Assessment, the research team will evaluate the causality between adverse events and interventions (34).

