### EA Group

Participants will receive 24 sessions of acupuncture treatment (three times a week for 6 weeks; 30 min a session; **Figure 2A**). According to traditional Chinese medicine theory, animal experiments (28, 29), and based on mutual consensus from clinical expert meetings, we will use acupoints GV20, GV29, and bilateral acupoints GB13 (**Figure 2B**) in the treatment. Disposable stainless steel needle insertion will be followed by performed stimulation, such as lifting and thrusting the needle combined with twirling and rotating the needle sheath (as shown in **Figures 2C**, **D**, the operation parameters of depth and frequency will be analyzed by acupuncture manipulation parameter tester [ATP-II; Shanghai Shangyou Medical Equipment Co. Ltd, Shanghai, China]), to produce the sensation known as deqi (sensation of numbness, soreness, radiating, or distention, which is considered to indicate effective needling) (30). One EA wire will be connected to the needle on acupoints GV20 and GV29, and another wire will be connected to the bilateral acupoints GB13. A continuous wave will be provided with a stimulation frequency of 2 Hz (31–33) and an intensity varied from 3 to 5 mA (34) until patients feel comfortable. Acupuncture will be performed by licensed acupuncturists with more than 3 years of clinical experience.

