In terms of clinical outcome assessment, we selected HAMD-17, BDI-II as the primary indicator, and SDS, SAS, and PSQI as the secondary indicators. HAMD-17 was developed by Max Hamilton in 1960 to assess the severity of depressive symptoms (51). BDI-II is a widely used assessment method to measure the presence and severity of depression-related symptoms (52). Therefore, we used HAMD-17 and BDI-II as the primary outcome indicators for assessing the degree and changes of depression in patients. SDS is a short self-assessment scale used to assess the psychological and physical symptoms of depression. It has been widely used for screening purposes and to measure depression in all ages (53). SAS was designed by William WK Zung in 1971 to evaluate the degree of anxiety in patients (54). PSQI is a widely used self-reported sleep questionnaire measure to assess sleep quality, including sleep duration, latency, efficiency, disorders, quality, and daytime dysfunction (55). Previous studies have found that patients with depression are often accompanied by symptoms of anxiety and insomnia (56). Therefore, we used SDS, SAS, and PSQI as secondary outcome indicators.

Some of the key technical issues that need to be addressed in this trial are: (1) in view of the current problems in the treatment of subthreshold depression, this study will explore whether acupuncture could be used as a new non-drug therapy to avoid the deterioration of subthreshold depression and promote the effect of counseling. (2) Determining the value and advantages of acupuncture treatment (effectiveness, onset time, duration of maintenance, side effects, patient compliance, and economic burden). (3) We will establish a biological sample bank before and after acupuncture treatment for patients with subthreshold depression for use in future research.

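### Adverse events are collected by participant-initiated report while therapy contacts differ at least threefold between arms, so the by-arm safety tables are open to ascertainment bias of unknown size

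*Protocol article*

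**What the plan says.** **Collection.** Under Safety and Adverse Events, the protocol article says: "The committee will remind participants to report any undesirable and unexpected experiences". Reports go to the research team at whatever point in the trial they arise, and relatedness to treatment is not required. For each event, "the time of occurrence, severity, management, and outcome of these adverse events will need to be recorded on the case report forms". The expected events listed there are all EA-related. The research team assesses causality.

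**Contacts.** The EA Group section says: "Participants will receive 24 sessions of acupuncture treatment (three times a week for 6 weeks; 30 min a session". The legend of Figure 2 gives the same weekly pattern ("3 times a week for 6 weeks; 30 min a session"). The Counseling Group receives "individual counseling (once a week for 6 weeks; 50–60 min a session". The Combination Therapy Group receives both.

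**Common assessments.** Outcome Measures sets assessments for every arm at weeks 2, 4 and 6 of treatment and lists the rating scales for them. It does not say whether adverse events are also asked about.

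**Blinding.** Only outcome evaluators and statistical analysts are blinded. Participants, physicians and data collectors are not.

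**Use of the data.** Statistical Analysis plans tabulations and descriptive statistics for safety. The Discussion counts among the attributes of acupuncture to be determined its "duration of maintenance, side effects, patient compliance, and economic burden".

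**The concern.** When events are recorded because a participant brings them up, the number recorded depends on how often the participant meets someone to tell. Here that frequency is set by the allocated treatment. A non-specific complaint that is equally common in all arms, such as headache, has more occasions to be mentioned in the two arms with EA. Two further features may add to the imbalance: the people who report and collect events know the allocation, and the list of expected events covers EA only.

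At stake is how the safety tables are read. The analysis is descriptive, but a table of events by arm will be used to judge side effects, and the Discussion makes side effects part of the case for or against acupuncture. An excess of general complaints in the EA arms could then reflect contact frequency as well as treatment. Later analysis cannot repair this, because events that were never mentioned cannot be recovered.

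**Working it through.** **Inputs from the article.** EA three times a week for 6 weeks, 30 minutes each; counseling once a week for 6 weeks, 50–60 minutes each; combination is both; three common on-treatment assessments (weeks 2, 4, 6). The article gives no adverse-event rate and no reporting probability.

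**Step 1: the article's own session count.** It states 24 EA sessions. Its schedule gives 3 × 6 = 18. The two do not agree in the EA Group and Combination Therapy Group sections, so both are carried forward.

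**Step 2: contacts by arm.** Counseling: 1 × 6 = 6 sessions, or 6 + 3 = 9 contacts if the assessments are separate visits.

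| Reading | EA | Combination | EA ÷ counseling | Combination ÷ counseling |
|---|---|---|---|---|
| Schedule, sessions only | 18 | 18 + 6 = 24 | 18/6 = 3.0 | 24/6 = 4.0 |
| Schedule, plus 3 assessments | 21 | 27 | 21/9 = 2.3 | 27/9 = 3.0 |
| Stated 24, sessions only | 24 | 24 + 6 = 30 | 24/6 = 4.0 | 30/6 = 5.0 |
| Stated 24, plus 3 assessments | 27 | 33 | 27/9 = 3.0 | 33/9 = 3.7 |

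The combination counts treat EA and counseling sessions as separate contacts. By time the imbalance is smaller: EA 18 × 30 = 540 minutes against 6 × 50 = 300 to 6 × 60 = 360 for counseling, a ratio of 540/360 = 1.5 to 540/300 = 1.8.

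**Step 3: what unequal contact could do (illustration on assumed values).** Suppose the true risk is the same in all arms and an event is mentioned with probability q at each contact. The share recorded after k contacts is 1 − (1 − q)^k. If an event can be mentioned only in the week after it occurs, k is 1 for counseling, 3 for EA and 4 for combination.

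| Assumed q | EA ÷ counseling | Combination ÷ counseling |
|---|---|---|
| 0.05 | (1 − 0.95³)/0.05 = 2.85 | (1 − 0.95⁴)/0.05 = 3.71 |
| 0.3 | (1 − 0.7³)/0.3 = 2.19 | (1 − 0.7⁴)/0.3 = 2.53 |
| 0.5 | (1 − 0.5³)/0.5 = 1.75 | (1 − 0.5⁴)/0.5 = 1.88 |
| 0.8 | (1 − 0.2³)/0.8 = 1.24 | (1 − 0.2⁴)/0.8 = 1.25 |

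If a complaint can be mentioned throughout the 6 weeks, the EA ratio at q = 0.5 is (1 − 0.5^18)/(1 − 0.5^6) = 1.02.

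**Step 4: relaxing equal q.** A counseling session is a longer one-to-one talk, so q may be higher there. Over 6 weeks, 10% per EA session gives 1 − 0.9^18 = 0.85, and 27% per counseling session gives 1 − 0.73^6 = 0.85. On those values the gap between EA and counseling disappears.

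**Step 5: after the fix.** Scheduled occasions on which events are asked about become 3 : 3 : 3.

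**The case against.** **The article may simply be silent.** It never says that the week 2, 4 and 6 visits exclude questions about events, and a condensed article commonly leaves such questions to the full protocol and the case report form. This stands, so the absence of a query schedule is not itself the point. The point is that the article does state a method, and that method gives unequal opportunity. If the full protocol already has a common question, one sentence resolves it.

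**No formal safety comparison is planned.** This stands. A reader might infer a planned between-arm test that is biased; Statistical Analysis supports only descriptive tables, and the comparative use comes from the Discussion.

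**Reporting is not tied to sessions.** Participants in every arm may report whenever they wish, and causality is assessed. Both soften the effect. Neither equalises the occasions for reporting, and a causality judgment cannot be made on an event that was never mentioned.

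**Mood and sleep are already measured equally.** This stands. HAMD-17, BDI-II, SDS and PSQI are taken in all arms at the same weeks. A reader might infer that worsening mood under counseling would go unseen; those scales argue against that. The point is confined to other complaints.

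**Needle events are real exposure.** This stands. Hematoma, fainting during acupuncture and needle faults arise only with needling, so an excess of them in the EA arms is not reporting bias.

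**The size rests on assumptions.** This stands: Steps 3 and 4 run from nearly threefold for EA alone to no gap.

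**Conclusion.** The point holds as a risk in the stated method. Therapy sessions differ by a factor of at least 3 against counseling (at least 2.3 if the assessments are separate visits), and reporting and collection are unblinded. The by-arm description of non-specific complaints outside the mood and sleep scales is therefore open to ascertainment bias. The likely direction is against EA, provided that the chance of mention per contact is not much higher in counseling.

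A reader might go further and conclude that the safety results are biased by a known amount. The article does not support that. It gives no reporting probability, and under near-complete reporting, long recall or a higher chance of mention in counseling the effect could be small or nil.

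Separately, the stated 24 EA sessions and the weekly schedule (18) contradict each other in two sections and must be reconciled. The contradiction does not change the direction of this point, but it affects any rate per planned session by a factor of 24/18 = 1.33.

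**What to change.** 1. Ask the same open adverse-event question, in fixed wording, in all three arms at the existing week 2, 4 and 6 assessments. Someone other than the blinded evaluator, for example the data collector, should ask it, so that answers about needling do not unblind the evaluator. If the full protocol already provides for this, say so in one sentence.
2. Base the by-arm description of general adverse events on those answers.
3. Tabulate needle-specific events separately, per session and per patient, in the two arms that receive EA.
4. Keep spontaneous reporting throughout for safety monitoring.
5. Reconcile the session count with the weekly schedule in the EA Group and Combination Therapy Group sections before any per-session rate is reported.

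The cost is one case-report-form item at three visits that already exist, a few minutes per visit, and one extra table. The change equalises the scheduled occasions for reporting. It does not blind participants or data collectors, so some influence of known allocation remains.
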